#### Primary

Ordinal logistic regression will be used to assess the difference in ‘Feedback and Advice’ *versus* ‘Advice Only’ group for motivation to prevent weight gain. Additional predictor variables will include age, gender and weight status at baseline, because these may influence results.

#### Secondary

Results from all secondary analyses will be considered as exploratory. One-way ANOVAs, followed by one-way ANCOVAs will be used to examine immediate psychological reactions to genetic test feedback in the sample overall once the AO group participants have received their genetic test results. Repeated-measures ANOVAs will be used to determine change in anthropometric measures within groups over time in the sample overall. Anthropometric differences between groups will be determined using one-way ANCOVA. Age, gender and baseline BMI will be included as covariates. Changes in diet quality, eating behavior and physical activity in the sample overall will be examined with repeated-measures ANOVAs. Changes between groups will be examined using one-way ANCOVAs, including age, gender and baseline BMI as covariates. Group differences in actual behavior change (as measured by adherence to the individual tips) will be assessed with a one-way ANCOVA. In addition, we will build an additive score of the total number of tips adhered to at least ‘occasionally’ and compare this in intervention and control group with a one-way ANCOVA. Age, gender and baseline BMI will be included as covariates. Bonferroni corrections will be used for multiple comparisons in all analyses. Within the ‘Feedback and Advice’ group, *FTO* status will be dichotomized into high/average risk, with those having at least one risk allele being classified as ‘higher-risk’. Ordinal regression analyses will be used to examine effects of risk status on motivation to control weight, as well as interactions between risk status and baseline BMI. Age and gender will also be included as predictor variables in the model. Finally, we will assess predictors of motivation to control weight with a multinomial regression analysis. We will include all potential predictors, including age, gender, *FTO* status, as well as stress, eating behavior, baseline BMI, and weight satisfaction.

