#### Secondary research objectives

The secondary objectives are to assess differences in adherence to the advice and weight change from baseline to eight month follow-up in those receiving genetic test feedback and weight gain prevention advice compared with advice alone. We hypothesize that participants receiving genetic test feedback, regardless of risk status, will be more adherent to the advice and gain less weight over the study period than those receiving weight gain prevention advice alone. Within the group of participants receiving feedback and advice, we will also explore psychological reactions immediately after receiving genetic test feedback, and interactions between weight status and gene test status. We hypothesize that those receiving a higher-risk genetic test result will show higher negative affect but not higher fatalism in response to their genetic test result compared to those receiving an ‘average-risk’ genetic test result. We also predict that overweight participants receiving a ‘higher-risk’ result will value having an explanation for their weight more than normal weight participants, and that overweight participants will be more motivated to prevent further weight gain in response to a higher-risk genetic test result than those receiving an ‘average-risk’ result. All secondary objectives are exploratory, because of limited power.

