#### Control group (‘Advice Only’ group)

Following baseline measurements, participants randomized to the ‘Advice Only’ control group will receive an email at the same time as the FA group informing them that they will receive their test result by the end of the academic year, resembling a ‘wait-list control’ group for the gene test feedback condition. The weight control advice leaflet will be attached to the email, matching the format of the intervention group. Ethical concerns about withholding weight control advice from individuals at increased risk of weight gain, and the likelihood of contamination between groups, led to the decision to send the leaflet to all participants and therefore not to have a ‘no treatment’ control group that receives neither leaflet nor genetic feedback. The gene test result will be sent out in identical format to the intervention group at the end of the academic year after collection of follow-up anthropometric data is complete.

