### Recruitment and consent

Ethical approval was granted by the University College London Research Ethics Committee for non-NHS research in September 2010. Participants will be recruited at the beginning of two consecutive academic years. Potential participants will be recruited through emails sent to all first year students (approximately 22,000) enrolled at University College London (UCL) inviting them to take part in a study where they will receive information on their personal genetic risk for weight gain susceptibility. A ‘collection station’ will be set up at UCL in the first two weeks of term where participants can receive detailed information about the study, check eligibility, enroll, and give saliva for DNA analysis. To ensure that participants are aware of the details of the study, information contained in the information sheet will be reiterated by a researcher. Participants will be told that the DNA analysis is only for one gene (*FTO*) which is related to a small increase in weight gain susceptibility and that students will be randomly allocated to receive their results either during term 2 (intervention group) or at the end of the academic year (control group). Participants will be informed that their samples will be destroyed on completion of the study and not stored for further analyses. Written consent will be obtained before participants give saliva for DNA analysis. The right to withdraw from the study without giving reason will be respected at all times, and saliva samples will be destroyed immediately after participant withdrawal.

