#### Secondary outcomes

Secondary outcomes are psychological reactions to genetic test feedback and actual behavior change as assessed by adherence to the individual weight control tips in the leaflet. Immediately after receiving genetic feedback (FA group after allocation, AO group after 8 months, see Figure 1), participants will complete a questionnaire concerning their psychological reactions using 18 items adapted from the vignette study by Meisel *et al*. [9]. One example is ‘Knowing my FTO gene test result provides me with an explanation for my body weight’ (strongly disagree to strongly agree).

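### The article names two different populations for the psychological-reaction analysis: the Feedback and Advice group in the objectives, both arms pooled in the analysis section

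*Protocol article*

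**What the plan says.** The Protocol article, Secondary research objectives, defines the reaction objective by group: "Within the group of participants receiving feedback and advice, we will also explore psychological reactions immediately after receiving genetic test feedback". The hypotheses that follow include that "those receiving a higher-risk genetic test result will show higher negative affect but not higher fatalism in response to their genetic test result", compared with average-risk recipients, and that overweight participants given a higher-risk result will value an explanation for their weight more than normal-weight participants.

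The Secondary part of Statistical analyses gives the model and another population: one-way ANOVAs and then one-way ANCOVAs are to "examine immediate psychological reactions to genetic test feedback in the sample overall once the AO group participants have received their genetic test results".

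The arms reach that questionnaire at different points. Secondary outcomes gives the timing as "FA group after allocation, AO group after 8 months, see Figure 1". Recruitment and consent says students are "randomly allocated to receive their results either during term 2 (intervention group) or at the end of the academic year (control group". The Control group section adds that AO results go out "at the end of the academic year after collection of follow-up anthropometric data is complete". The advice leaflet goes to both arms at the same time, so AO already hold it when their result arrives, whereas FA receive it with theirs.

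**The concern.** One outcome has two stated analysis populations, and they are not interchangeable. FA participants react to a result received during the year in which weight gain is expected, together with the advice. AO participants react after that year, after a wait for the result, and after being weighed again. The reaction may be the same in both settings, but nothing in the article establishes that.

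Two things are at stake. If the effect of a higher-risk result differs between settings, the pooled contrast describes neither of them, and the planned output would not show the difference. And with both populations in print, either the FA-only or the pooled result could be reported as the planned one after both have been seen.

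**Working it through.** The article gives no effect size, power or sample size for the reaction analysis, so there is no figure of its own to reproduce.

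**Text check**

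| Item | Objectives | Analysis section |
|---|---|---|
| Population | FA group | FA and AO together |
| Contrast | Higher-risk v average-risk result; weight status among higher-risk recipients | One-way; factor not named |
| Arm in the model | Not needed | Not mentioned |

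A one-way model has a single factor. If that factor is risk status, arm is not a second factor. If it is arm, the model does not test the risk-status hypotheses. That arm is absent is an inference from the wording, since the factor is not named.

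**What pooling estimates**

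Let d_FA and d_AO be the higher-risk minus average-risk differences in SD units, and w the FA share of responders.

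- Pooled difference = w × d_FA + (1 − w) × d_AO
- With 50% responding in both arms, w = 0.50/(0.50 + 0.50) = 0.50
- With 50% in FA and 30% in AO (assumed), w = 0.50/0.80 = 0.625

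**Illustration**

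Inputs from the article: 252 participants with a risk allele and 148 without, per arm of 400 (Randomization); about half lost to follow-up measures (Minimizing drop out). Assumptions: the same 50% loss applies to the reaction items in both arms, and d_FA = 0.4.

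- SE for FA alone (126 v 74) = √(1/126 + 1/74) = 0.146 SD
- SE pooled (252 v 148) = √(1/252 + 1/148) = 0.104 SD
- Detectable difference at 80% power, two-sided 5% = 2.80 × SE: 0.41 SD for FA alone, 0.29 SD pooled
- At 40% retention (the 60% attrition in Sample size and assumptions), the same formula gives 0.46 and 0.32 SD

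Power = Φ(d/SE − 1.96). FA alone with d = 0.4: 78%. Pooled, at 50% retention in both arms:

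| Assumed d_AO | Pooled difference | Pooled power |
|---|---|---|
| 0.4 | 0.40 | 97% |
| 0.2 | 0.30 | 83% |
| 0 | 0.20 | 49% |
| −0.2 | 0.10 | 16% |

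**What an arm term or an interaction test adds**

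- Omitting an arm main effect costs little precision. An arm shift of 0.3 SD (assumed) raises residual variance by 0.3²/4 = 2.25%, and the SE by about 1.1%.
- An arm-by-risk test has SE = √(0.146² + 0.146²) = 0.207 SD. For 0.4 v 0.2 SD, power = Φ(0.2/0.207 − 1.96), about 16%.

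What the plan lacks is therefore mainly the separate estimates by arm. An interaction p-value would add little.

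**The case against.** Pooling may be deliberate and is defensible. The article schedules the AO reaction questionnaire, cites limited power for its secondary objectives, and expects heavy attrition. The same section restricts the motivation-by-risk analysis to FA, so the authors wrote that restriction when they wanted it. In the illustration pooling has more power than FA alone when the AO effect equals the FA effect (97% v 78%) and even when it is half as large (83% v 78%). Model terms are often left to a fuller plan, and the analysis is exploratory.

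Most of this stands. It justifies keeping a pooled analysis and treating the point as minor. It does not remove the conflict: the article states both populations, so this is not a detail left to another document.

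A reader might go further in three ways that the article does not support.

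- **Pooling biases or confounds the genotype contrast.** Allocation is random and made before DNA analysis, so arm is independent of genotype. Pooling estimates an average over two delivery times, apart from any differential non-response.
- **The reaction ANCOVA uses an out-of-date baseline BMI for AO.** The sentences naming age, gender and baseline BMI follow the anthropometric, diet and activity, and adherence analyses. None is attached to the reaction ANCOVA.
- **AO participants would be put in the wrong weight-status group.** The article does not say when weight status is taken for this hypothesis and gives no figure for changes of category. FA are also weighed before their term 2 result.

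**Conclusion.** The point holds as an inconsistency between the objectives and the analysis section, with a pooled model that, as worded, would not show whether the effect of a higher-risk result depends on when it is received. How far the pooled estimate departs from the FA effect is unknown: not at all if the two effects are equal, and half of the FA effect if AO has none and response is equal. Those AO values are assumptions, not figures from the article.

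Only the reaction hypotheses (negative affect, fatalism, valuing an explanation) are touched. The primary outcome, adherence and weight change are compared between arms, and the motivation-by-risk analysis stays within FA. Severity is minor.

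**What to change.** - State in both sections which population tests the reaction hypotheses. The objectives name FA.
- Keep the pooled analysis as supportive, name its factors, and include arm (timing of the result) as one of them.
- Report the higher-risk v average-risk estimates with confidence intervals separately for FA and AO. An arm-by-risk term may be shown descriptively, with a note that its power is low and that a null result would not show that timing is irrelevant.

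The cost is a few sentences and one degree of freedom in the pooled model. No new data are needed, because the AO reaction questionnaire is already planned, and with recruitment still in progress the change can be made before analysis. The drawback is the wider FA-only interval shown in the working; the pooled result would still be reported beside it.

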**Methods/design:**

First-year university students (n = 800) will be randomized to receive either 1) their personal genetic test result for a gene *(FTO)* related to weight gain susceptibility in addition to a leaflet with simple weight control advice (‘Feedback + Advice’ group, FA), or 2) only the leaflet containing simple weight control advice (‘Advice Only’ group, AO).

Motivation to avoid weight gain and active use of weight control strategies will be assessed one month after receipt of the leaflet with or without genetic test feedback. Weight and body fat will be measured at baseline and eight months follow-up. We will also assess short-term psychological reactions to the genetic test result. In addition, we will explore interactions between feedback condition and gene test status.

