### Randomization

All consenting participants will be randomized to ‘FA’ (intervention) or ‘AO’ (control) after baseline data collection is complete and records have been anonymized using serial numbers. For group allocation, we will use the randomization function in the Statistical Package for Social Sciences (SPSS 19 for Windows®; SPSS Inc., Chicago, IL, USA), which randomly assigns a set percentage of cases to a specified number of groups. Each group will consist of 400 participants, and based on population frequencies of *FTO* we expect 252 to have at least one higher-risk (A) allele and 148 to have the lower-risk (TT) genotype. Randomization will take place after data collection of each wave is complete, but before the DNA analyses are conducted. Experimenter bias is unlikely, as records are anonymous and not easily identifiable. Although neither researchers nor participants will be blind to group allocation, follow-up weights will be measured objectively and print-out records kept, which excludes inadvertent manipulation of records. Questionnaire data will be collected online, which minimizes the risk of missing data or inadvertent manipulation.

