#### Baseline questionnaire

The baseline questionnaire will be sent by email after anthropometric data and saliva have been collected. It will include demographic and health-related measures (age, gender, course of study, year of study, family history of overweight), and standardized questionnaires assessing the following: *Diet quality* will be determined using the using the DINE, which is a self-report food frequency questionnaire, commonly used in clinical practice, assessing dietary fat, fiber and fruit and vegetable content [29]. *Eating behavior* will be assessed with the Dutch Eating Behavior Questionnaire (DEBQ), which determines tendencies for emotional eating, restraint eating and external eating [30]. *Physical activity* will be assessed with the Recent Physical Activity Questionnaire (RPAQ), which assesses time and frequency for a range of physical activities for commute and leisure [31]. *Stress* will be determined using the Perceived Stress Scale-4 (PSS-4, [32]. The PSS-4 is a short version of the 20-item perceived stress scale, with good psychometric properties [33]. Four items will assess *worry about weight gain*[34] and *diet self-efficacy*[35]. All questionnaires have sound psychometric properties and are commonly used in clinical practice.

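### The between-arm ANCOVAs of change in diet, eating behavior and activity adjust for baseline BMI but not for the baseline of the score analysed, which costs some precision

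*Protocol article*

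**What the plan says.** The Secondary part of Statistical analyses names the covariates for these between-arm comparisons.

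- Diet quality, eating behavior and physical activity: "Changes between groups will be examined using one-way ANCOVAs, including age, gender and baseline BMI as covariates".
- Anthropometry: "Anthropometric differences between groups will be determined using one-way ANCOVA. Age, gender and baseline BMI will be included as covariates".

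Neither list contains the baseline value of the outcome being compared, yet those values are collected. The abstract says of the body measurements: "Weight and body fat will be measured at baseline and eight months follow-up". DINE, DEBQ and RPAQ are part of the baseline questionnaire: "The baseline questionnaire will be sent by email after anthropometric data and saliva have been collected". The Randomization section places allocation after baseline data collection, so all of these are pre-randomization variables.

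The Secondary research objectives describe the weight outcome as "weight change from baseline to eight month follow-up". The same section and the Secondary analysis section both call the secondary work exploratory, and the former gives limited power as the reason.

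**The concern.** Baseline BMI is the outcome's own baseline only when BMI is the outcome. For a fat-intake, dietary-restraint or activity score it is likely to be a weak stand-in. A change score without its own baseline in the model still carries regression to the mean: participants who start high tend to fall and those who start low tend to rise, and this adds noise to the comparison. The same omission leaves a chance imbalance in that baseline only partly corrected among the half or fewer of participants expected to return.

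What is at stake is precision. The protocol already regards power for secondary questions as limited and plans Bonferroni corrections on top. The covariates are fixed in the text rather than left open, so an analyst following the plan would forgo a gain that the collected data allow.

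**Working it through.** **The plan's own figure.** None exists for these analyses. The stated n = 340 concerns the primary outcome and is not used here.

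**Inputs from the protocol article.** Sample 800, allocated 400 per arm (Randomization). Attrition 60% (Sample size and assumptions), so 800 x 0.4 = 320 analysed; or about half (Minimizing drop out), so 800 x 0.5 = 400. The significance level is 5%, taken here as two-sided.

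**Assumptions; the document gives none of these.**
- r: correlation of the outcome between baseline and follow-up.
- c: correlation of the outcome's baseline with baseline BMI.
- Equal outcome variance at both visits, set to 1, and BMI related to follow-up only through the outcome's own baseline.
- A difference of 0.25 SD for the power illustration.

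**Residual variance under each model.**
- Change score adjusted for BMI: 2(1 - r) - [(1 - r)c]^2
- Follow-up value adjusted for BMI: 1 - (rc)^2
- Either outcome adjusted for its own baseline: 1 - r^2

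With c = 0, the ratio of own-baseline to change-score variance is (1 - r^2) / [2(1 - r)] = (1 + r)/2, that is 0.70 at r = 0.4 and 0.90 at r = 0.8.

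**Diet, eating and activity (change, c = 0.2).** Example at r = 0.5: 2(0.5) - (0.5 x 0.2)^2 = 0.990 with BMI; 1 - 0.25 = 0.750 with own baseline; ratio 0.758.

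| r | Change, BMI-adjusted | Own baseline | Ratio |
|---|---|---|---|
| 0.4 | 1.186 | 0.840 | 0.71 |
| 0.5 | 0.990 | 0.750 | 0.76 |
| 0.6 | 0.794 | 0.640 | 0.81 |
| 0.7 | 0.596 | 0.510 | 0.86 |
| 0.8 | 0.398 | 0.360 | 0.90 |

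The saving is therefore about 10-29%, or 10-30% if BMI is given no credit.

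**Power at 0.25 SD.** The standard error is sqrt(4 x variance / N). At N = 320 and r = 0.5 it is sqrt(4 x 0.990 / 320) = 0.111 with BMI, giving 61% power, and sqrt(4 x 0.750 / 320) = 0.097 with own baseline, giving 73%.

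| r | N = 320 | N = 400 |
|---|---|---|
| 0.5 | 61% to 73% | 71% to 82% |
| 0.6 | 71% to 80% | 80% to 88% |
| 0.7 | 82% to 88% | 90% to 94% |

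These figures ignore the planned Bonferroni correction, which would lower both columns of each pair.

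**Weight and body fat.** The ratio of own-baseline to BMI-adjusted variance depends on which outcome is meant.

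| Outcome | c | r | Ratio if change | Ratio if follow-up value |
|---|---|---|---|---|
| Weight | 0.85 | 0.95-0.98 | 0.993-0.997 | 0.28-0.13 |
| Body fat | 0.75 | 0.90-0.95 | 0.98-0.99 | 0.35-0.20 |

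The saving is about 0.3-2% for change, and 65-87% for follow-up values.

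**The case against.** The best case for the plan is that leaving out a prognostic covariate does not bias a randomized comparison, that every secondary analysis is declared exploratory, and that the gain is smallest for the outcome most readers care about. All of this stands and limits the weight of the point. In addition, diet, eating and activity, where the gain is clearest, are not named among the secondary objectives or in the Secondary outcomes section; they appear in the analysis section.

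Several stronger readings are tempting, and the document does not support them.

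- **That the weight analysis loses most of its precision.** A reader might infer a several-fold inflation of variance, since BMI leaves height variation in follow-up weight. That holds only if raw follow-up weight is compared. The objectives name weight change, for which height cancels and the loss is under 1%. The wording "Anthropometric differences between groups will be determined using one-way ANCOVA" leaves the matter open, so the large figure is conditional.
- **That the questionnaire analyses should be judged against follow-up scores alone.** The plan says changes are examined, so the 10-30% comparison is the relevant one.
- **That the fix would also strengthen the behavior-change outcome.** That outcome is adherence to the leaflet tips, and no baseline measure of it is listed.
- **That recruitment wave is a serious omission.** Allocation is done by wave ("Randomization will take place after data collection of each wave is complete") and no model includes it, but the gain cannot be computed from the document and is probably small.
- **That the primary model needs changing.** It states: "Additional predictor variables will include age, gender and weight status at baseline". Preferring continuous BMI there is a matter of taste, and nothing in the document shows a loss of any given size.

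**Conclusion.** The point holds as a modest loss of efficiency. For change in diet quality, eating behavior and physical activity, the stated covariates forgo about 10-30% of residual variance. In the example with 320 analysed, a 0.25 SD difference and r = 0.5, that is worth about 12 percentage points of power. The range rests on assumed correlations of 0.8 to 0.4 and equal variances at both visits; the direction of the gain is the same throughout that range.

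For weight and body fat the practical problem is that the outcome is not pinned down. The omission is negligible if change is analysed and large if follow-up values are compared. Where BMI itself is the outcome, baseline BMI is already the right covariate.

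The validity of the randomized comparison and the primary analysis are not affected.

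**What to change.** In the Secondary analysis section, add to each between-arm ANCOVA the baseline value of the outcome it compares: the DINE, DEBQ or RPAQ score for that same score, baseline weight for weight, and baseline body fat for body fat. Keep age and gender. With the own baseline in the model, analysing change or the follow-up value yields the same treatment estimate, so this also settles the anthropometric ambiguity; even so, say which of the two will be reported.

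Leave the tip-adherence analysis as it is. Including wave is optional. No change to the primary model is called for.

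The cost is a change of wording. All the variables are already collected, and a change score needs the same baseline value, so relative to that analysis no participant is lost. Recruitment is described as in progress, so the change can be recorded before outcomes are analysed.

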#### Adherence to the weight loss tips

Adherence to the weight loss tips will be assessed by asking: ‘How often in the last month did you… (watch portion sizes, avoid second helpings, slow down your eating, avoid eating mindlessly/focus on your food, pass up extra snacks between meals, avoid sweet drinks or chose a lite drink, integrated some physical activity into your day)’*.* Response options were given on a Likert scale, ranging from ‘never’ to ‘always’*.*

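### Tip adherence is called behavior change, but the items are described only at follow-up and no baseline value enters the ANCOVA

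*Protocol article*

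**What the plan says.** The Secondary outcomes section of the protocol article defines one outcome as "actual behavior change as assessed by adherence to the individual weight control tips in the leaflet". The analysis section headed Secondary keeps that label: "Group differences in actual behavior change (as measured by adherence to the individual tips) will be assessed with a one-way ANCOVA".

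The instrument is described under Follow-up, in the section on adherence to the tips, which opens "Adherence to the weight loss tips will be assessed by asking". It asks how often in the last month the participant did each of seven things. Five are "watch portion sizes, avoid second helpings, slow down your eating, avoid eating mindlessly/focus on your food, pass up extra snacks between meals"; the other two concern sweet drinks and physical activity. Answers run on a Likert scale from never to always.

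The Baseline questionnaire section itemizes its content: "It will include demographic and health-related measures (age, gender, course of study, year of study, family history of overweight), and standardized questionnaires". The instruments it then names are the DINE, DEBQ, RPAQ and PSS-4, plus four items on worry about weight gain and diet self-efficacy. The seven tip items are not among them.

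For the adherence analyses, "Age, gender and baseline BMI will be included as covariates". A second version of the outcome is a count: "we will build an additive score of the total number of tips adhered to at least" occasionally.

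**The concern.** The items describe ordinary habits and do not refer to the leaflet. A student who already ate modest portions, avoided sweet drinks and exercised before the leaflet arrived will score as highly adherent at follow-up without having acted on it. One post-leaflet rating measures a level. It cannot separate a habit taken up from a habit kept.

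Two things are at stake. One is wording: a report of behavior change based on this score would claim more than the data show. The other is precision: stable differences between people in these habits stay in the error term, because the model contains no starting value of the behavior.

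**Working it through.** **Figure to reproduce.** None. The article states no effect size, SD or power for adherence; its power calculation concerns the primary outcome.

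**Label against measurement.**
- Label: change (Secondary outcomes; analysis section headed Secondary).
- Time points described for the seven items: follow-up only.
- Baseline value in the model: none.
- Comparison within the plan: diet quality, eating behavior and physical activity have baseline instruments, and the plan gives them repeated-measures analyses of change. With no starting value described, the tips cannot be analyzed that way.

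**What the scores can distinguish.** Student A answers always before and after the leaflet. Student B moves from never to a middle category. On the item scale A scores above B, although only B changed. On the count, both score 1 for that tip if B's answer reaches occasionally. Neither version identifies the change.

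**Does the missing baseline bias the arm comparison?** This was checked with 4,000 simulated trials: 160 per arm, true difference 0.25 SD, baseline-to-follow-up correlation 0.5, complete data. The mean estimate was 0.249 (SE 0.112) from follow-up alone and 0.248 (SE 0.097) with baseline adjustment. The Monte Carlo error of the first mean is 0.112/√4000 = 0.002, so both agree with 0.25. The loss is in precision, not validity.

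**Size of the precision loss.** Inputs:
- 400 per arm (Randomization).
- Attrition of 60% (Sample size and assumptions) or about 50% (Minimizing drop out), leaving 400 × 0.4 = 160 or 400 × 0.5 = 200 per arm.
- r, the correlation of baseline and follow-up tip score given age, gender and BMI. This is not in the article and is assumed to be 0.3 to 0.6.
- A difference of 0.25 residual SD and two-sided 5% alpha, for illustration only.

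Formulas: variance removed = r²; equivalent sample factor = 1/(1 − r²); SE in SD units = √(1 − r²) × √(2/n); power = Φ(0.25/SE − 1.96).

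| r | Variance removed | Sample factor | SE, n = 160 | Power, n = 160 | SE, n = 200 | Power, n = 200 |
|---|---|---|---|---|---|---|
| none (current plan) | 0% | 1.00 | 0.112 | 61% | 0.100 | 71% |
| 0.3 | 9% | 1.10 | 0.107 | 65% | 0.095 | 75% |
| 0.4 | 16% | 1.19 | 0.102 | 68% | 0.092 | 78% |
| 0.5 | 25% | 1.33 | 0.097 | 73% | 0.087 | 82% |
| 0.6 | 36% | 1.56 | 0.089 | 80% | 0.080 | 88% |

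The table assumes that everyone analyzed has a baseline score.

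**The case against.** **The comparison is randomized and meets the objective.** This stands. The secondary objective is a between-arm difference in adherence, with the hypothesis that the feedback arm will be more adherent. A reader might infer that the missing baseline biases the result or defeats the objective. The documents do not support either inference: randomization protects the contrast at follow-up, and the objective does not require within-person change in the tips.

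**The trial does measure change.** This also stands. A reader might infer that the trial cannot say whether anyone changed behavior. That goes too far, because change in diet quality, eating behavior and physical activity is analyzed overall and between arms, using baseline instruments that overlap with several tips. The gap concerns the tip score itself.

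**Existing weight controllers are excluded.** Partly. Students who have controlled their weight for more than a month are left out of the analysis, which removes some established habits. It does not remove students who exercise or avoid sweet drinks for other reasons.

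**The published baseline list may be incomplete.** Fair. Weight satisfaction is a planned predictor in the analysis section, yet it is missing from the baseline list too. It is therefore not proven that the tip items go uncollected at baseline. Even if they are collected, the stated covariates do not use them.

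**The gain is uncertain.** Fair. No correlation is given. Enrollment is in the first two weeks of term, so a last-month question at baseline largely covers life before university, whereas feedback follows in term 2 and most students live in catered halls. The lower end of the range is plausible. A ceiling on the count could weaken the correlation further.

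**Conclusion.** The point holds as one of labelling and efficiency. As described, the outcome is the frequency of seven behaviors at follow-up. It is called change, it credits habits held before the leaflet, and its model omits what is likely to be a strong covariate.

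Adjustment would be worth between 1.10 and 1.56 times the analyzed sample for a partial correlation of 0.3 to 0.6, with the lower end plausible. This rests on the assumed correlation, on near-complete baseline forms among those analyzed, and on the published baseline list being accurate for these items.

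All secondary analyses are declared exploratory and no power is claimed for adherence, so the priority is low to moderate.

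**What to change.** 1. In every intake still open, add the seven items to the baseline questionnaire, before randomization. The form already exists: "The baseline questionnaire will be sent by email after anthropometric data and saliva have been collected". Enter each item's baseline value as a covariate in its ANCOVA, and the baseline total in the analysis of the count.
2. For intakes enrolled without the items, use the related baseline DEBQ, DINE and RPAQ scores as covariates for adherence.
3. Unless baseline items are available for the whole analyzed sample, use one name for the outcome in all intakes, such as frequency of the recommended behaviors at follow-up, and do not report it as behavior change.

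The cost is about a minute of extra questionnaire time, some early exposure to the behaviors (equal in both arms because it precedes randomization), and the added covariates. The change of name costs nothing. Recruitment spans two academic years and is reported as in progress, so the first step is possible only for intakes whose baseline is still to be collected.
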